### Assessments During the Trial

The presence of risk factors associated with raised BP and cardiovascular risk are determined using standardized questionnaires in face-to-face interviews performed by staff members with undergraduate degrees in nutrition, biomedicine, or biology. Evaluations are performed at the beginning and end of the study using standardized interviews on prior morbidity, drug use, eating habits, and lifestyle. At the clinic, measurements are taken of weight; height; waist, hip, and neck circumferences; estimated body composition (bioelectrical impedance analysis); electrocardiography; retinography; and laboratory evaluation of cholesterol and fractions, triglycerides, fasting glucose, glycated hemoglobin A_1c_, creatinine, potassium, C-reactive protein, and urinary sodium. At home, measurements are taken of capillary glucose (before breakfast and dinner for 3 days; Accu-Chek glucose meter, Roche Diabetes Care Inc) and step count (Omron HJ-112 digital pocket pedometer, Omron Healthcare Inc) during the waking hours for 7 days. Participants have BP recorded in the office using an automatic oscillometric device and at home using a Spacelabs 90207 monitor (Spacelabs Healthcare).

In addition, participants are instructed not to change doses or type of antihypertensive medication during the trial.

### Sample Size Calculation and Statistical Analysis

The sample size calculation is based on results from a prior RCT with a factorial design [5]. Table 2 shows simulations for sample size calculations maintaining constant 80% power and 95% confidence interval. The largest sample size was obtained for a BP reduction of 6.8 [SD 13.1] mm Hg on 24-hour systolic BP in the intervention group compared to 3.4 [SD 11.6] mm Hg in the usual care treatment. Therefore, a sample of at least 222 participants is necessary to test our hypothesis.

Trial results will be analyzed using the intention-to-treat approach. The effectiveness of the active interventions will be tested in comparison to the control group. A pooled analysis of the differences between the active interventions versus control will be performed if there is no interaction. For continuous variables, the assumptions to use *t* tests will be verified using the Shapiro-Wilks test (for normal distribution) and the Levene test (for homogeneity of variance), and equal variances are assumed. Therefore, baseline characteristics will be analyzed using the *t* test for independent samples and chi-square test for categorical variables. Generalized estimating equations models will used to analyze the group, time, and time × group differences. The relative risk will be used to determine the corresponding relative risk reduction. *P*<.05 will be considered statistically significant, and .05<*P*<.15 will be considered a trend toward association.

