**Results:**

This study was funded by two Brazilian agencies: the National Council for Scientific and Technological Development and Fundação de Amparo à Pesquisa do Estado do Rio Grande do Sul. Enrollment was completed at the end of 2017 (N=231), the follow-up is ongoing, and data analysis is expected to begin in early 2019. A reduction of 24-hour systolic BP of approximately 8.8 [SD 13.1] mm Hg for participants in the BP monitoring group versus 3.4 [SD 11.6] mm Hg in the UCT group is expected. A similar reduction in the text messaging group is expected.

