**Weight loss**			
	Reduction of at least 3 kg and average reduction		X

^a^Reduction or increase is calculated based on baseline and end of trial assessments.

**Table 2 table2:** Sample size calculations based on a previous trial [5] and additional simulations maintaining constant 80% power and 95% confidence interval.

Intervention-to-control ratio	Average reduction in the intervention group, mm Hg (SD)	Average reduction in the control group, mm Hg (SD)	Calculated sample size per group	Total sample size
1:1:1:1	8.8 (13.1)	3.4 (11.6)	31	124
1:1:1:1	7.8 (13.1)	3.4 (11.6)	39	156
1:1:1:1	6.8 (13.1)	3.4 (11.6)	51	204
1:1:1:2	8.8 (13.1)	3.4 (11.6)	44/22	132
1:1:1:2	7.8 (13.1)	3.4 (11.6)	56/28	168
1:1:1:2	6.8 (13.1)	3.4 (11.6)	74/37	222

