## Discussion

### Lowering Blood Pressure

Hypertension is an inexorable and progressive condition that has deleterious effects on the heart, brain, and vascular system. Reducing BP and increasing control of hypertension are the main targets of interventions. However, if possible, the best intervention should be that which doesn’t require additional BP-lowering medications. Thus, any intervention capable of lowering BP or increasing BP control and, at the same time, attenuating other cardiovascular risk factors could represent an advantageous step in treatment.

This trial is the first to comprehensively compare two strategies for reducing BP and risk factors in cardiovascular disease. Results from previous trials have indicated the potential beneficial impact of self-monitoring programs [23], home blood pressure monitoring [5], and text messages [24], but these interventions have not been compared or assessed regarding other cardiovascular risk factors. The sample size, although larger than other trials, might be a limitation to test the secondary hypothesis.

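### Table 2 matches a calculation that leaves out the 3.4 mm Hg control reduction, so 222 participants do not give 80% power at 6.8 versus 3.4 mm Hg

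*Protocol article*

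**What the plan says.** Under Sample Size Calculation and Statistical Analysis the article states: "Table 2 shows simulations for sample size calculations maintaining constant 80% power and 95% confidence interval". It describes the adopted scenario in these words: "BP reduction of 6.8 [SD 13.1] mm Hg on 24-hour systolic BP in the intervention group compared to 3.4 [SD 11.6] mm Hg in the". The comparator there is UCT. From this it concludes: "Therefore, a sample of at least 222 participants is necessary to test our hypothesis".

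Table 2 lists six rows. Each sets an intervention reduction of 8.8, 7.8 or 6.8 mm Hg (SD 13.1) beside a control reduction of 3.4 mm Hg (SD 11.6). Equal allocation gives 31, 39 and 51 per group. Unequal allocation gives 44/22, 56/28 and 74/37. The last row totals 222.

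The Results part of the abstract shows that the two reductions belong to separate arms: "approximately 8.8 [SD 13.1] mm Hg for participants in the BP monitoring group versus 3.4 [SD 11.6] mm Hg in the UCT group is expected". The main Results section repeats this contrast.

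The analysis text tests the active interventions against control, and pools them against control if there is no interaction. The Discussion makes one concession on size: "The sample size, although larger than other trials, might be a limitation to test the secondary hypothesis".

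**The concern.** A two-arm comparison of mean reductions is sized on the difference between the arms. The article's figures make that difference 5.4, 4.4 or 3.4 mm Hg. With SDs of 11.6 to 13.1, 51 per group looks far too few for 3.4 mm Hg.

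If the sizes were worked out on a larger difference, the stated 80% power does not exist at the scenario chosen to justify the trial's size. Readers would then give a non-significant primary result more weight than it can bear, because the Discussion confines the size limitation to the secondary hypothesis.

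**Working it through.** **Inputs.** Reductions, SDs, 80% power and the 95% confidence level come from Table 2 and the sample size section. The allocation 1:1:2:1 comes from Study Design, and N=231 from the abstract. The article does not state sidedness; two-sided 5% is assumed. Then (1.960 + 0.842)² = 7.849, 13.1² = 171.61 and 11.6² = 134.56.

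**Formulas.**
- 1:1, per group: n = 7.849 × (171.61 + 134.56) / d² = 7.849 × 306.17 / d²
- 2:1 intervention to control, control arm: n = 7.849 × (134.56 + 171.61/2) / d² = 7.849 × 220.365 / d²

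**Step 1: reproduce the printed sizes.** Set d to the intervention arm's own reduction.

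| d (mm Hg) | 1:1 computed | Table 2 | 2:1 control computed | Table 2 |
|---|---|---|---|---|
| 8.8 | 31.03 | 31 | 22.33 | 22 (with 44) |
| 7.8 | 39.50 | 39 | 28.43 | 28 (with 56) |
| 6.8 | 51.97 | 51 | 37.41 | 37 (with 74) |

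All six rows agree after truncation.

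**Step 2: use the stated differences.**

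| d (mm Hg) | 1:1 computed | needed per group | 2:1 control computed | needed (intervention/control) |
|---|---|---|---|---|
| 8.8 − 3.4 = 5.4 | 82.4 | 83 | 59.3 | 120/60 |
| 7.8 − 3.4 = 4.4 | 124.1 | 125 | 89.3 | 180/90 |
| 6.8 − 3.4 = 3.4 | 207.9 | 208 | 149.6 | 300/150 |

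In the adopted row d was doubled (6.8 for 3.4), so the size is short by a factor of about four.

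**Step 3: power of the printed sizes.** Power = Φ(d/SE − 1.96), with SE = √(171.61/n₁ + 134.56/n₀). For 74 versus 37, SE = 2.44; at d = 3.4 power is about 29%. For 51 versus 51 it is about 28%. At their true differences the 8.8 rows have about 40% and the 7.8 rows about 35%.

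**Step 4: power with 231 enrolled.** Assume about 46/46/92/46 under 1:1:2:1 and no loss to follow-up. For a factorial main effect stratified by the other factor, the common variance is (171.61 + 134.56)/2 = 153.1. The stratum weights are 46×46/92 = 23.0 and 92×46/138 = 30.7, so SE = √(153.1/53.7) = 1.69.

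| Comparison | SE | power at 3.4 | power at 5.4 |
|---|---|---|---|
| Single arm vs UCT (46 vs 46) | 2.58 | 26% | 55% |
| Combined arm vs UCT (92 vs 46) | 2.19 | 34% | 69% |
| All active arms pooled vs UCT (184 vs 46) | 1.96 | 41% | 79% |
| Factorial main effect, no interaction | 1.69 | 52% | 89% |

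**Step 5: other readings of Table 2.** Keeping d = 3.4 at 1:1, a one-sided 5% test needs 164 per group, a two-sided 15% test needs 138, and halving the per-arm size for a factorial margin needs 104. The printed figure is 51. To make 51 right at d = 3.4, the SD would have to be 3.4 × √(51/2) / 2.802 = 6.1, against a pooled 12.4 from the stated SDs.

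**The case against.** The strongest objections concern what is built on the arithmetic.

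- **How low the power is.** A reader might take 25% to 35% as the power of the trial. That range covers only arm-versus-UCT tests at 3.4 mm Hg. The design is factorial and a pooled analysis is planned; these reach 41% and 52%. The objection stands as to scope, but none of these comparisons reaches 80% at the adopted scenario.
- **What a null would mean.** A reader might infer that a null is the likely result even if the interventions work as expected. The expected effect is 8.8 against 3.4, a difference of 5.4 mm Hg, where power is 55% to 89%. Of these two scenarios, a null is more likely than not only at 3.4 mm Hg, and there only for the arm-versus-UCT and pooled tests.
- **The primary comparison.** It is tempting to make the factorial main effects primary because they alone exceed 80% at 5.4 mm Hg. The documents do not support this. The Introduction compares three strategies with usual care and expects the combination to beat single interventions, which main effects do not test. The 89% also needs no interaction, and enrolment has closed.
- **The mechanism is inferred.** The article nowhere says the control reduction was dropped, and the match requires truncating 39.50 and 51.97 where rounding up is usual. That is fair. But the mismatch between inputs and sizes stands without any explanation of how it arose.
- **The arm sizes are assumed.** 46/46/92/46 sums to 230. Table 2 labels its ratio 1:1:1:2, and the blocks of 4 and 8 do not fit a ratio summing to five. With four equal arms of about 58, single-arm power would be roughly 31% at 3.4 and 65% at 5.4. The conclusion is unchanged.

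Nor does the condensed format of an article explain this. The inputs, the table and the conclusion are all printed, and they disagree.

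**Conclusion.** The point holds in this form. Table 2's sizes do not follow from its stated means and SDs at 80% power, and the claim that 222 suffices at 6.8 versus 3.4 mm Hg is wrong. The sizes behave as if the control reduction were zero; this is a strong diagnosis from six matching rows, not something the article documents.

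The shortfall depends on the comparison and on the true effect, so no single power figure describes the trial. At the adopted scenario every comparison examined falls well below 80%. At the expected effect, single-arm and combined-arm tests against UCT fall short, the pooled test comes close, and main effects exceed 80% if there is no interaction.

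These figures assume two-sided 5%, the stated SDs, the inferred arm sizes, no multiplicity adjustment and no loss. The article gives no loss rate. If loss were 10% to 20%, main-effect power would be about 48% to 44% at 3.4 mm Hg and 86% to 82% at 5.4 mm Hg.

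**What to change.** 1. Recompute Table 2 with differences of 5.4, 4.4 and 3.4 mm Hg, and state sidedness and rounding.
2. Withdraw the statement that 222 participants give 80% power at 6.8 versus 3.4 mm Hg.
3. Restate power for the 231 enrolled, separately for each arm versus UCT, pooled active arms versus UCT, and the factorial main effects. Use the actual arm sizes and label the assumptions on loss and interaction.
4. Extend the Discussion's sample-size limitation to the primary comparisons.

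Do not change the primary comparison on power grounds.

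The cost is a corrected table, a short paragraph and a less favourable power statement. No participants, visits or data are added. According to the abstract, analysis had not begun when the article appeared, so the correction could precede it.

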### Randomization and Allocation Concealment

A computer-generated sequence was created in the random allocation software [22], which is used to randomly assign participants to 1 of 4 groups using permuted random block sizes of 4 and 8. The randomization sequence was generated prior to the trial initiation and is kept in the Research Electronic Data Capture software, which releases the allocated group only after completion of the enrollment. Just after completion of the enrollment of a participant, the randomized group is released, preventing the research team from anticipating to which arm the next participant will be allocated. Follow-up visits are scheduled for 7, 30, 90, and 180 days from randomization. At the 7-day visit, participants in the intervention groups can address any problems with image capture or text messages. The protocol was registered in the Plataforma Brasil (CAAE: 31423214000005327), a condition to be submitted to the Ethics Committee. It was approved by the Ethics Committee of the Hospital de Clinicas de Porto Alegre (GPPG number 16-0187), which is accredited by the Office of Human Research Protections as an institutional review board. After the institutional approval, the protocol was registered with ClinicalTrials.gov [NCT03005470]. A written informed consent is obtained from all participants according to the principles expressed in the Declaration of Helsinki. Potentially eligible participants will be evaluated in 3 consecutive clinical visits, held in the morning, in order to confirm eligibility criteria.

**Table 1 table1:** Description of clinical and laboratory outcomes and their definitions.

Outcomes and definitions^a^		Primary outcome	Secondary outcomes

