**Blood pressure**			
	Reduction in 24-hour systolic blood pressure in ambulatory blood pressure monitoring	X	
	Reduction in 24-hour diastolic blood pressure in ambulatory blood pressure monitoring		X
	Reduction in daytime systolic blood pressure		X
	Reduction in nighttime systolic blood pressure		X
	Office BP control (<130/80 mm Hg) [21]		X

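### The planned group × time GEE on baseline and end-of-trial 24-hour systolic BP is a comparison of mean changes; adjusting for baseline would be more precise at no cost

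*Protocol article*

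**What the plan says.** The primary outcome in Table 1 of the protocol article is "Reduction in 24-hour systolic blood pressure in ambulatory blood pressure monitoring". The table's footnote fixes the time points: "Reduction or increase is calculated based on baseline and end of trial assessments". In Randomization and Allocation Concealment, "Follow-up visits are scheduled for 7, 30, 90, and 180 days from randomization", but the article states no ambulatory monitoring at the intermediate visits.

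The model is named in Sample Size Calculation and Statistical Analysis: "Generalized estimating equations models will used to analyze the group, time, and time × group differences". The same section plans comparisons of the active interventions with control, and a pooled comparison if there is no interaction.

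A raised 24-hour ambulatory BP is an entry criterion (Study Participants), so every randomised participant has a baseline value of the primary measure.

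**The concern.** A time term is possible with two ambulatory readings only if the baseline reading is part of the response. The treatment effect is then the time × group coefficient, which subtracts each arm's baseline mean in full. Because baseline and final BP are imperfectly correlated, a full subtraction is more than the data support: an arm that happens to start high will tend to fall further for that reason alone. The cost is a wider confidence interval and, in any one trial, an estimate that carries part of the chance baseline difference.

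This matters because the arms are small (231 participants at 1:1:2:1 is about 46 in each single-intervention arm and in control) and enrolment is closed. The analysis is the main remaining means of gaining precision.

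**Working it through.** **Inputs from the article.** SDs of change 13.1 (intervention) and 11.6 (control). Sizing scenario: "6.8 [SD 13.1] mm Hg on 24-hour systolic BP in the intervention group compared to 3.4 [SD 11.6] mm Hg in the usual care treatment", a difference of 6.8 − 3.4 = 3.4 mm Hg. Expected scenario: "approximately 8.8 [SD 13.1] mm Hg for participants in the BP monitoring group versus 3.4 [SD 11.6] mm Hg in the UCT group", a difference of 8.8 − 3.4 = 5.4 mm Hg. N = 231, allocation 1:1:2:1, so 231/5 = 46.2 per share. The sample size section works with "maintaining constant 80% power and 95% confidence interval", read here as two-sided alpha 0.05.

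**Input not in the article.** The correlation r between baseline and end-of-trial 24-hour systolic BP is not given, nor is the SD of the BP itself. Every result that depends on r is therefore shown over a range.

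**The plan's own figure.** For two means, n(control) = (11.6² + 13.1²/k)(1.96 + 0.84)²/difference². For the 2:1 row (k=2) and a difference of 3.4 this gives about 150 controls, not the 37 in Table 2. The table's 37 (and 6 × 37 = 222) appears only if 6.8 itself is used as the difference, which gives 37.4. At 74 versus 37 and a true difference of 3.4, power is about 29%. That is a separate defect. It is noted here because it means the trial has less power than stated.

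**Step 1: the named model is a change-score comparison.** In simulated complete two-point data, the GEE time × group coefficient equalled the difference in mean change to rounding error, under both independence and exchangeable working correlation. Adding baseline BP as a main-effect covariate to this model does not alter the coefficient, because a time-invariant term cancels from the within-person change.

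**Step 2: relative precision.** With a common SD s at both times:
- Var(change) = 2s²(1−r)
- Var(baseline-adjusted) = s²(1−r²)
- ratio = (1+r)/2, so the share removed is (1−r)/2

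Simulated ratios were 0.69, 0.74 and 0.87 at r = 0.4, 0.5 and 0.7, against 0.70, 0.75 and 0.85 in theory. Both estimators averaged about −3.4 when the true difference was −3.4, so neither is biased.

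**Step 3: power, one single-intervention arm versus usual care.** Unadjusted variance = (13.1² + 11.6²)/46.2 = 306.17/46.2 = 6.627, SE 2.574. Power = Φ(difference/SE − 1.96). The adjusted SE is 2.574 × √((1+r)/2).

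| r (assumed) | variance removed | SE | power at 5.4 | power at 3.4 |
|---|---|---|---|---|
| change score | – | 2.574 | 55.5% | 26.1% |
| 0.4 | 30% | 2.154 | 70.8% | 35.1% |
| 0.5 | 25% | 2.229 | 67.8% | 33.2% |
| 0.6 | 20% | 2.303 | 65.0% | 31.4% |
| 0.7 | 15% | 2.373 | 62.4% | 29.9% |
| 0.8 | 10% | 2.442 | 59.9% | 28.5% |
| 0.9 | 5% | 2.509 | 57.6% | 27.3% |

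For the combined arm (92.4) versus usual care (46.2), power goes from 70% to 77–84% at 5.4 mm Hg and from 34% to 39–46% at 3.4 mm Hg (r = 0.7 to 0.4).

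**Step 4: chance imbalance.** At r = 0.5 the article's change SDs imply a BP SD of √(153.085)/√(2 × 0.5) = 12.37 mm Hg. One standard error of the baseline difference at 46.2 per arm is 12.37 × √(2/46.2) = 2.57 mm Hg. A baseline difference of that size moves the change-score contrast by (1 − 0.5) × 2.57 = 1.3 mm Hg, against a sizing difference of 3.4.

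**The case against.** The strongest reply is that this is a condensed article, its one sentence on the GEE does not exclude covariates, and a covariate list is normally left to the analysis plan. That would settle the matter if the point were a missing covariate. It does not settle it here: within a group, time and time × group model on two readings, adding baseline leaves the treatment estimate unchanged (Step 1). The gain needs a different model, so the point concerns what is stated.

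Four stronger readings are tempting, and the article supports none of them.

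- *That the analysis is biased.* Eligibility thresholds apply to all arms alike, so regression to the mean is equal in expectation. Chance imbalance is part of the sampling variance of an unbiased estimator.
- *That a known 15–30% of precision is lost.* That range is r = 0.7 to 0.4, which nothing in the article establishes. At r = 0.9 the loss is 5%.
- *That adjustment would rescue the trial's power.* At 3.4 mm Hg it does not. The planned pooled active-versus-control comparison (184.8 versus 46.2, SE 1.96) already has about 79% power at 5.4 mm Hg without adjustment.
- *That the baseline t and chi-square tests will decide what is adjusted for.* The article says only that baseline characteristics will be tested.

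It also stands that the equality with the change score is exact only for complete two-point data. Missing final readings, or ambulatory readings at further visits, would alter it.

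**Conclusion.** The point holds as a free improvement, not as an error. On complete data the stated model compares mean change between arms, which is valid but less precise than a baseline-adjusted comparison. The removable share of variance is (1−r)/2, from 30% at r = 0.4 to 5% at r = 0.9. For r between 0.7 and 0.4, power for one single-intervention arm versus usual care goes from about 55% to 62–71% at 5.4 mm Hg and from about 26% to 30–35% at 3.4 mm Hg.

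These figures rest on an assumed r, equal BP variance at both times, the article's SDs of change, an exact 1:1:2:1 split of 231, no loss to follow-up, and a normal approximation with two-sided alpha 0.05.

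**What to change.** Keep the stated comparisons with control, and reword the primary analysis as a model of end-of-trial 24-hour systolic BP on randomised group with baseline 24-hour systolic BP as covariate. An equivalent choice is a repeated-measures model in which baseline means are constrained equal across arms. If fitted by likelihood, it also retains participants whose final reading is missing, under a missing-at-random assumption. Use the same approach for each continuous secondary outcome that has a baseline value. Settle the wording before the data analysis begins.

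The cost is a change of analysis wording. Baseline ambulatory BP is already collected for everyone, and no new data, visits or participants are required.

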Innovative technologies can be used to achieve BP reduction, but it remains unknown if interventions should be focused only on hypertension control or should address lifestyle as well. Therefore, the purpose of this study is to compare the effectiveness of 3 strategies to reduce systolic BP assessed by ambulatory BP monitoring and improve lifestyle in comparison to the usual care of patients with hypertension (usual clinical treatment [UCT], control group). Our hypothesis is that participants assigned to active interventions will achieve greater BP reduction than those in the control group. The intervention by text messaging (TELEMEV) is a stimulus for adoption of a healthy lifestyle that may reduces BP, while telemonitoring of BP (TELEM) can enhance adherence to antihypertensive medication and stimulate healthy lifestyle. In addition, we hypothesized that participants who receive the combined intervention (TELEM+TELEMEV) will obtain greater reduction in BP than those submitted to individual interventions.

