## Methods

### Study Design

This is a factorial RCT (Figure 1) of effectiveness of the use of technologies—mobile phones and BP monitoring—to reduce systolic BP and change lifestyle. Figure 2 shows that participants are randomly allocated to 1 of 4 groups: telemonitoring BP (TELEM), telemonitoring messages (TELEMEV), telemonitoring BP plus telemonitoring messages (TELEM+TELEMEV), or UCT, with an allocation ratio of 1:1:2:1.

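### The plan labels results with P between .05 and .15 a trend, on the primary outcome as on any other, although such P values say little about whether an effect exists

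*Protocol article*

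**What the plan says.** All of this is in the protocol article.

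- **Thresholds** (Sample Size Calculation and Statistical Analysis): "P*<.05 will be considered statistically significant". The same sentence goes on to the next band: "05<*P*<.15 will be considered a trend toward association". The rule names no outcome or comparison to which it is limited.
- **Comparisons** (same section): "The effectiveness of the active interventions will be tested in comparison to the control group", and "A pooled analysis of the differences between the active interventions versus control will be performed if there is no interaction".
- **Aims** (Introduction): "the purpose of this study is to compare the effectiveness of 3 strategies to reduce systolic BP", each set against usual care. A further hypothesis is that participants given both interventions "will obtain greater reduction in BP than those submitted to individual interventions".
- **Allocation** (Study Design): TELEM, TELEMEV, combined and UCT, "with an allocation ratio of 1:1:2:1".
- **Primary outcome** (Outcomes and Their Assessment; Table 1): 24-hour systolic BP on ambulatory monitoring.

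**The concern.** A P value between .05 and .15 is a non-significant result. The plan commits in advance to describing it as pointing towards an association, whichever outcome it concerns. If no intervention works, this raises the chance that the report contains encouraging language about the primary outcome. If an intervention does work, a result in the band is still weak evidence, and an estimate with its confidence interval would describe it better.

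This is not an omission that an unseen analysis plan could fill. The article states the rule itself.

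**Working it through.** **No figure to reproduce.** The article gives no overall error rate. Its stated values are the two thresholds, .05 and .15. Sidedness is not stated. I assume two-sided tests, in keeping with the sample-size basis of "maintaining constant 80% power and 95% confidence interval".

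**1. One test, no effect.** P is then uniform, so Pr(P<.05) = 5%, Pr(.05<P<.15) = 15% − 5% = 10%, and Pr(either label) = 15%. Half of each lies in the favourable direction: 2.5%, 5% and 7.5%.

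**2. Three active arms against UCT, no effect in any arm.**

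- Arm sizes: the 231 enrolled (Abstract, Results) split 1:1:2:1 give 46.2, 46.2, 92.4 and 46.2. The article does not report actual arm sizes.
- The tests share the UCT arm. The correlation of two of them is √[(n_i/(n_i+n_0))·(n_j/(n_j+n_0))]. This is √(½·½) = 0.50 for TELEM with TELEMEV, and √(½·⅔) = 0.58 for the combined arm with either.
- Critical |z| is 1.960 at .05 and 1.440 at .15. Simulating the joint null distribution (at least 1,000,000 draws) gives:

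| At least one of three | Either direction | Favouring the intervention |
|---|---|---|
| P<.05 | 12.1% | 6% |
| P<.15 (significant or trend) | 32.8% | 16.4% |

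If the tests were independent, the either-direction figures would be 1 − 0.95³ = 14.3% and 1 − 0.85³ = 38.6%. Table 2 also considers 1:1:1:1 and 1:1:1:2. Those ratios give 33.8% and 36.4% for P<.15 in either direction, so the result depends little on the ratio.

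**3. How informative is the band?** Table 2 assumes reductions of 8.8, 7.8 or 6.8 (SD 13.1) against 3.4 (SD 11.6), that is, differences of 5.4, 4.4 or 3.4 mm Hg. With the arm sizes above:

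- SE = √(13.1²/46.2 + 11.6²/46.2) = 2.574 for a single arm against UCT.
- SE = √(13.1²/92.4 + 11.6²/46.2) = 2.184 for the combined arm against UCT.
- With t = difference/SE, Pr(P<α) = Φ(t − z) + Φ(−t − z), where z is the critical value for α.

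| Difference | Arm | t | Pr(P<.05) | Pr(P<.15) | Pr(in band) |
|---|---|---|---|---|---|
| 5.4 | single | 2.098 | 55.5% | 74.5% | 19.0% |
| 5.4 | combined | 2.473 | 69.6% | 84.9% | 15.3% |
| 4.4 | single | 1.709 | 40.1% | 60.7% | 20.6% |
| 4.4 | combined | 2.015 | 52.2% | 71.8% | 19.6% |
| 3.4 | single | 1.321 | 26.2% | 45.6% | 19.4% |
| 3.4 | combined | 1.557 | 34.4% | 54.8% | 20.4% |

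A result in the band is therefore 15.3/10 = 1.5 to 20.6/10 = 2.1 times as likely under the hoped-for effect as under none. For P<.05 the same ratio is 26.2/5 = 5.2 to 69.6/5 = 13.9.

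These powers lie below the 80% in Table 2. That is a separate matter, and the error rates in steps 1 and 2 do not depend on it. If power really were 80%, then t = 1.960 + 0.842 = 2.802 and Pr(in band) = Φ(2.802 − 1.440) − 0.80 = 91.3% − 80% = 11.3%, hardly different from the 10% under no effect.

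**The case against.** The best defence is that the plan keeps its two labels apart. Only P<.05 is called statistically significant, and no section says that a trend will count as proof of effectiveness. That is correct, and it rules out several stronger readings that a reader might infer.

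- **That the significance level becomes 15%.** It does not. The 15% is the chance of either label. The chance of a significant result in one test stays at 5%.
- **That there is a one-in-three chance of a claim in favour of the interventions.** The 33% includes results where an active arm does worse than UCT. The stated hypothesis is directional, and the favourable share is about 16%.
- **That the comparisons will be tested without adjustment.** The article does not say so. It is silent, and a condensed article may leave adjustment and test order to the analysis plan. An overall group test at .05 as a gatekeeper would hold the P<.05 figure to about 5% when no arm has an effect. Whether distinct arms sharing a control need adjustment is also debated.
- **That combined against each single arm belongs in the same family.** Adding those two tests would give 44% (27% in the favourable direction). But the Introduction adds that hypothesis after the main one, and the Discussion speaks of a secondary hypothesis for which the sample may be too small. The larger figures should not be the headline.
- **That trends will be used to support policy.** The Results section mentions public health policy but does not link it to the trend label.

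It could also be argued that direction makes the band more informative: favourable band results are about 15% to 21% likely under the assumed effects against 5% under none, a ratio of about 3 to 4. That is fair, but it is still weak evidence, and a confidence interval conveys it without a label.

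**Conclusion.** The concern holds as a point about the trend rule. The rule is explicit, unrestricted, and reaches the primary outcome. With no true effect it triples the chance of a labelled result in a single test, from 5% to 15%. Across three comparisons with UCT it raises the chance of at least one label from about 12% to 33% in either direction, or from about 6% to 16% in favour of the intervention. The single-test figure needs only a two-sided test. The three-comparison figures further assume 1:1:2:1 arm sizes, no effect in any arm, and no adjustment or gatekeeping. They cover the primary outcome at one time point. The finding that the band is uninformative rests on Table 2's differences and SDs at the enrolled size.

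The multiplicity question is secondary. The article's silence on adjustment is not itself an error. The problem affects interpretation and reporting, not the validity of the estimates.

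**What to change.** Delete the trend clause. In its place, state that each between-group difference will be reported with its 95% confidence interval and exact P value, and that only P<.05 will be called statistically significant.

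It would also help to say which comparison or comparisons on 24-hour systolic BP are confirmatory. This is advisable but secondary. Whether to adjust across arms is for the analysis plan.

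The cost is one clause, with no effect on sample size, data or trial conduct. The only loss is that borderline results can no longer carry the trend label. The article reports follow-up as ongoing, with analysis expected to begin in early 2019, so on its own timetable the change could be made before analysis.
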